## Abstract

**Background:**

Depression is the leading cause of disability in youth, with a global economic burden of US >$210 billion annually. However, up to 70% of youth with depression do not receive services. Even among those who do access treatment, 30% to 65% fail to respond and many dropout prematurely, demonstrating a need for more potent, accessible interventions. In a previous trial, a single-session Web-based growth mindset (GM) intervention significantly reduced depressive symptoms in high-symptom adolescents; however, this intervention did not benefit adolescents uniformly. For instance, the intervention reduced depression in adolescents who reported post intervention increases in perceived control, but it did not lead to significant depression reductions in adolescents who reported no significant post intervention increases in perceived control.

**Objective:**

The goal of this project is to test the acceptability and efficacy of a novel, single-session, virtual reality (VR) depression intervention—the *VR Personality Project*—teaching GM, the belief that personal attributes are malleable rather than fixed. The VR Personality Project was designed to systematically target and increase adolescents’ perceived control by offering a more immersive, engaging, user-directed intervention experience than the Web-based intervention can provide. By targeting an identified predictor of intervention response, the VR Personality Project may lead to larger reductions in depressive symptoms than existing Web-based mindset interventions.

**Methods:**

Adolescents with elevated depressive symptoms or a recent history of depression (N=159; ages 12 to 16 years) will be randomized to one of 3 intervention conditions: the VR Personality Project; the Web-based GM intervention tested previously; or an active, Web-based control. Adolescents and their parents will report on the adolescents’ depression symptoms, perceived control, and related domains of functioning at preintervention, postintervention, and at 3- and 9-month follow-up assessments.

**Results:**

We predict that the VR and Web-based mindset interventions will both lead to larger reductions in adolescent symptoms than the control intervention. Additionally, we predict that the VR-based single session intervention will lead to larger reductions in depression than the online mindset intervention and that these symptom reductions will be mediated by increases in adolescents’ perceived control from pre- to postintervention.

**Conclusions:**

The results may suggest an efficient strategy for reducing adolescent depressive symptoms: One that is mechanism-targeted, relatively affordable (less than US $200 for a commercially available VR headset, a fraction of the cost of long-term psychotherapy) and potentially engaging to adolescents experiencing mood-related distress.

**Trial Registration:**

ClinicalTrials.gov NCT0385881; https://clinicaltrials.gov/ct2/show/NCT03858881 (Archived by WebCite at http://www.webcitation.org/78C3roDgA).

**International Registered Report Identifier (IRRID):**

DERR1-10.2196/13368

## Introduction

### Background

Psychiatric disorders are the leading cause of disability worldwide, and 40.5% of this burden is attributable to depressive symptoms and disorder. Levels of depressive symptoms increase markedly in adolescence with nearly 20% of the youth experiencing a depressive disorder between ages 12 and 18 years [1]. Adolescent-onset depression accounts for 66% of lifetime depression cases and predicts interpersonal problems, substance abuse, and a 20-fold increased risk of attempting suicide. Despite this early onset and protracted course, up to 70% of adolescents with depression symptoms and disorders do not receive services [2-4]. Even among those who do access psychosocial or medication-based treatment, 30% to 65% fail to respond [5] and many drop out of clinic-based services prematurely—after 3.9 sessions on average [6]. These findings highlight the urgent need for more potent and accessible interventions for adolescent depression.

Emerging work suggests that single-session interventions (SSIs) can increase accessibility of potent interventions for youth depressive symptoms and disorders [7]. SSIs include core elements of comprehensive, evidence-based treatments, but their brevity makes them easier to disseminate to diverse settings. Indeed, SSIs can successfully treat youth psychiatric problems: In a meta-analysis of 50 randomized trials [4], SSIs for youth psychological problems demonstrated significant beneficial effects (mean *g*=.32) across various levels of youth problem severity, suggesting the potential of SSIs for youths with diagnosable and subclinical psychopathology. Furthermore, significant effects emerged even for self-administered (eg, Web-based) interventions (mean *g*=.32). Notably, SSIs’ overall effects are slightly smaller than those observed for multisession psychotherapy [8]. However, their high potential to render services more scalable and accessible—especially for youths who might otherwise go without services entirely—could magnify their benefits for youth psychological health on a large scale.

One SSI in particular has shown promise in reducing adolescent depressive symptoms: the growth mindset (GM) SSI, which encourages youths to view traits and attributes as malleable (a GM) as opposed to unchangeable (a *fixed mindset*). Youths holding fixed mindsets of personal traits tend to report higher levels of psychopathology [9] and increased internalizing problems over time [10,11]. Recent research suggests that encouraging GMs via brief, targeted interventions can help shift this trajectory: 30- to 90-min self-administered GM SSIs have prevented adolescent depression symptoms in nonclinical samples (OR=.55, with the GM group showing lower odds of reporting clinically elevated levels of depression 9 months later [12]). In a randomized controlled trial (RCT) targeting high-symptom adolescents, a GM SSI led to postintervention increases in adolescents’ perceived control over behavior (*d*=.34, *P*<.001) and emotions (*d*=.19, *P*=.03) relative to a comparison (supportive therapy [ST]) SSI [13]. The GM SSI also predicted steeper 9-month declines in youth depression symptoms per parent (*B*=–0.99, *P*=.047) and adolescent reports (*B*=–1.37, *P*=.03) [14].

Although multiple versions of GM SSIs have been developed to fit varying settings and populations, they are generally self-administered by youths; teach the *brain science* behind why it is possible for a trait (eg, personality, loneliness, and anxiety) to change; include testimonial quotes from peers reinforcing the possibility of personal change; and involve the completion of at least one *self-persuasion* exercise wherein youths write about how change is possible to help a peer who is struggling [15]. Thus, the GM SSI may help remove barriers to adolescents asking for help and for expanding effort rather than withdrawing in the face of setbacks and failure.

Despite its promising effects, it is notable that the GM SSI does not reduce depression in all adolescents. For instance, in the most relevant RCT, the GM SSI reduced depressive symptoms in adolescents who reported postintervention increases in perceived control over their personal behaviors, but it did not lead to significant depression symptom reductions in adolescents who reported small or no increases in perceived control [16]. Thus, the potency of GM SSIs for adolescent depression has yet to be optimized. Such potency may be advanced by developing new iterations of GM interventions (GMIs), which are designed to more systematically target predictors and mechanisms of clinical outcomes, such as low levels of perceived control: a predictor and risk factor for depression [17-21] that GM SSIs have successfully mitigated, both in the short-term [13] and over time [14]. Such efforts may increase the promise of GMIs to produce larger, longer lasting symptom reductions for a greater proportion of youth.

### Objectives

Accordingly, the goal of this 3-arm RCT is to evaluate the acceptability and efficacy of a novel, single-session virtual reality (VR)-based GM SSI—the *VR Personality Project* —for depressive symptoms in adolescents compared with both a Web-based GM-SSI and an active, Web-based control program. Immersive VR creates interactive, computer-generated worlds, which substitute real-world sensory perceptions with digitally generated ones, producing the sensation of actually being in new life-sized environments. The last 2 decades have seen a significant increase in the use of VR technology in mental health interventions, with research suggesting benefits of VR-mediated interventions for various anxiety disorders, specific phobias, posttraumatic stress disorder, substance use, and eating disorders [22-27], largely through graded exposure to feared stimuli and situations. VR has also been extended to the adjunctive treatment of psychotic symptoms, delivering cognitive rehabilitation, and social skills training interventions in ecologically valid virtual environments [28,29]. For this study, the VR Personality Project was designed in collaboration with Limbix Inc to systematically target and increase adolescents’ sense of perceived control by offering a more immersive, active, and user-directed intervention experience than Web-based GM SSIs have provided. Within the VR program, participants can exert control over their intervention experience by actively engaging with *characters* in the VR world, autonomously navigating through various environments and speaking directly to (eg, offering verbal advice) same-aged *peers*. By strengthening adolescents’ interactions with the program content, lessons, and characters and providing a more ecologically valid environment (relative to that offered by a computer-based program) for youths to rehearse and apply newly acquired skills, the *VR Personality Project* may engage an identified predictor of response to GM SSIs in turn producing larger reductions in depression than Web-based versions. Thus, the *VR Personality Project* may represent a mechanism-targeted, efficient strategy for reducing adolescent depression: one that is both relatively affordable (less than US $200 for any commercially available VR headset; a fraction of the cost of long-term psychotherapy) and potentially engaging to adolescents experiencing mood-related distress.

Notably, a recent systematic review of studies evaluating VR applications for mental health identified only 2 studies that have tested immersive VR mental health treatment approaches; both were uncontrolled feasibility trials targeting adults [19]. Thus, to our knowledge, this study will be the first randomized trial evaluating a brief VR intervention for adolescent depressive symptoms.

This research has 4 specific aims. Our first aim is to replicate past research suggesting that GM SSIs can significantly reduce depressive symptoms in at-risk adolescents. We hypothesize that adolescents aged 12 to 16 years who participate in a GMI (Web-based *or* VR–based) will show larger reductions in depression symptoms from baseline through the 9-month follow-up assessment compared with adolescents who receive an active, Web-based control program.

Our second aim is to evaluate new, single-session, VR GMI including a comparative efficacy study. Our second aim is to also evaluate whether the new VR–based GM SSI (the VR Personality Project) can reduce depressive symptoms in adolescents, both relative to an active control program and to the previously tested Web-based GM SSI [13,14]. We hypothesize that adolescents who participate in the VR–based GM SSI will show larger reductions in depressive symptoms from baseline through the 9-month follow-up assessment compared with adolescents who receive the Web-based GMI *and* compared with adolescents who receive the active Web-based control program.

Our third aim is to test whether shifts in perceived control mediate intervention effects on adolescent depressive symptoms. The VR Personality Project was designed to target and increase adolescents’ perceived control by offering a more immersive, active, and user-directed intervention experience than the Web-based GM SSI can provide. Thus, the third goal of this study is to examine whether the VR Personality Project does, in fact, reduce adolescent depressive symptoms by eliciting proximal increases in perceived control. We hypothesize that the VR Personality Project will lead to larger increases in immediate postintervention perceived control than the Web-based intervention from pre- to postintervention and that these increases will mediate subsequent reductions in adolescent depression across the follow up period.

Our fourth aim is to gauge acceptability of the VR intervention. Adolescents’ perceptions of any intervention can impact completion rates, program engagement, and ultimately intervention effectiveness. Thus, an additional aim of this research is to examine whether adolescents view the VR Personality Project as more engaging, helpful, and interesting than the Web-based GMI or the Web-based control intervention.

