#### Web-Based Supportive Therapy

The Web-based ST [13,14] intervention, called the Sharing Feelings Program, is delivered entirely via Qualtrics, is self-administered by youths, and takes approximately 30 min to complete. It is structurally similar to the Web-based GMI, but it is designed to mimic ST. The goals of the ST intervention are to encourage youths to identify and express feelings to close others; the intervention does not teach or emphasize specific skills or beliefs. In a previous trial, ST led to smaller improvements in adolescent stress recovery, perceived control, and internalizing problems compared with a GM program [13,14]. The ST SSI is designed to control for nonspecific aspects of intervention, including engagement in a computer program. It includes the same number of reading and writing activities as the Web-based mindset intervention; it also mirrors the Web-based mindset intervention’s structure, including vignettes written by older peers describing times when they benefited from sharing feelings with close others. Immediately following intervention completion, all youths (regardless of condition assignment) will be asked to complete the same battery of questionnaires immediately postintervention to index immediate shifts in proximal outcomes.

After both the youth and the parent have completed their respective portions of the study, the laboratory visit will conclude. All study participants will be offered referral information for psychotherapy and/or pharmacologic treatment at Stony Brook and the surrounding community. Participants will not be excluded from completing study procedures if they begin receiving treatment for psychological distress during the study.

Before the youth and parent leave the laboratory, study personnel will inspect the youth and parent questionnaire responses on items inquiring about suicidal ideation. If there is any indication of adolescent suicidal ideation during the laboratory session, risk assessments will be conducted by trained study personnel. In the event that a participant is in imminent danger to themselves or others, their accompanying parent will be informed. Study personnel will meet with the family to establish a safety plan. In the event of reported, active suicidal ideation or plan, the family will be accompanied to the Psychiatric Emergency Program at the nearby University Hospital.

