## Results

### Aim 1: Attempt to Replicate Past Research

We will use mixed-effects linear models to test the hypothesis that interventions teaching GM (either VR or Web-based) predict reductions in adolescent depressive symptom severity (primary study outcome), per both adolescent and parent reports, relative to Web-based ST. Our study design, including 3 assessment points is structured to allow for detection of linear intervention effects. We will run additional mixed-effects linear models to assess whether interventions teaching GM predict larger improvements in secondary study outcomes (perceived primary and secondary control, hopelessness, loneliness, attitudes toward psychotherapy, and parent psychopathology) versus Web-based ST. Intervention condition will be a binary predictor variable in these models, with the VR GMI and Web-based GMI groups collapsed into a single *GM* intervention group. Potential covariates will include family income, age, sex, and time (baseline, postintervention where applicable, and 3-month and 9-month follow-up); each possible covariate will be included in analyses if it shows a significant association with a model outcome at baseline or any follow-up point (such associations are unlikely to occur, given randomization procedures, but remain possible). Models will include a random intercept and slope, an autoregressive error structure, and use full information maximum likelihood (FIML) estimation to address missing data. We will create 2 orthogonal planned contrasts for testing intervention effects. One planned contrast will examine whether the 2 active GM conditions differ from the ST control condition, whereas the other planned contrast will examine whether the VR-based intervention outperforms the Web-based intervention. A significant (*P*<.05) interaction between the first contrast and time would indicate that interventions teaching GM predicted significantly different 9-month change in an outcome relative to the control ST condition. We will also replicate these analyses for the most central symptoms of adolescent depression identified in previous analyses (*sadness*, *self-hatred*, and *loneliness*) and use Holm-Bonferroni corrections for multiple comparisons.

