### Aim 2: Evaluate New, Single-Session, Virtual Reality Growth Mindset Intervention

As for Aim 1, we will use mixed-effects linear models to test the hypothesis that VR-GMI predicts greater reductions in adolescent and parent-reported depressive symptom severity (primary study outcomes), as well as perceived primary and secondary control, hopelessness, loneliness, attitudes toward psychotherapy, and parent psychopathology (secondary outcomes), relative to (1) the Web-based GM program, (2) the control program, and (3) either program, when combined into a single, *non-VR intervention* group. Models will be structured as described in Aim 1. A significant (*P*<.05) interaction between the second orthogonal contrast mentioned in Aim 1 and time would indicate that interventions teaching GM predicted significantly different 9-month change in an outcome relative to the control ST condition. We will also replicate these analyses for the most central symptoms of adolescent depression identified in previous analyses (*sadness*, *self-hatred*, and *loneliness* [43]) and use Holm-Bonferroni corrections for multiple comparisons.

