### Aim 3: Test Mediation Through Perceived Control

To test whether the VR intervention and the Web-based GM intervention reduces youth-reported depressive symptoms through proximal increases in perceived control, we will conduct multiple mediation analyses which involve simultaneous indirect effects by multiple variables [44]. This approach allows for both an analysis of the total indirect effect (the aggregate indirect effect of all the candidate mediators under investigation) and analyses of specific indirect effects (ie, of each mediator under investigation). For mediation models assessing perceived control, we will use postintervention data to assess candidate mediators and 9-month follow-up data to assess depressive symptoms. In each model, the predictor variable will be intervention condition (in Model 1, VR versus Web-based GM intervention; in Model 2, VR versus Web-based ST; and in Model 3, Web-based GM versus Web-based ST); the simultaneous mediator variables will be postintervention perceived behavioral control and postintervention perceived emotional control. We will use bias-corrected bootstrapping to test the significance of specific and total indirect effects within the mediation model. Bootstrapping has the advantage of high statistical power without assuming multivariate normality in sampling distributions, enabling parsimonious analysis of one or several candidate mediators [44,45]. The Iavaan package version 0.5-16 in R version 2.15.1, which is capable of testing both multiple and single mediator models using FIML estimation, will be used for mediation tests [46]. To test for indirect effects of candidate mediators, parameter estimates of total and specific indirect effects are generated, along with their CI, using 1000 to 20,000 random bootstrapped samples. We will specify 5000 resamples in this study per Preacher and Hayes’ [32] recommendations. If the 95% bias-corrected CI for a total indirect parameter estimate does not contain 0, then that indirect effect can be considered statistically significant, demonstrating mediation [44,45]. Using this approach, this study will be sufficiently powered to detect significant indirect effects in each model (bias-corrected CIs for a 2-mediator model show .80 power for samples of 50 and over .90 for samples of 100 [46,47]).

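### Aim 3's hypothesis of a larger immediate gain in perceived control with VR than with Web GMI has no declared test that matches it; the declared contrast-by-time test can dilute or reverse such a gain

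*Protocol article*

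**What the plan says.** The third aim, under Objectives, has two parts. The first is that VR "will lead to larger increases in immediate postintervention perceived control than the Web-based intervention from pre- to postintervention"; the second is that these increases mediate later reductions in depression.

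Under Aim 2, perceived control is analysed by mixed model: depressive symptoms are the primary outcomes, "as well as perceived primary and secondary control, hopelessness, loneliness, attitudes toward psychotherapy, and parent psychopathology (secondary outcomes". The VR-versus-Web comparison is carried by the "interaction between the second orthogonal contrast mentioned in Aim 1 and time". Its significance is read as having "predicted significantly different 9-month change in an outcome relative to the control ST condition". (That reading names the wrong comparator, since the second contrast is VR against Web GMI. The slip should be corrected, but the quantity named is still 9-month change.)

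Aim 2 takes its model structure from Aim 1. There the time variable is "time (baseline, postintervention where applicable, and 3-month and 9-month follow-up", and the design is described as "structured to allow for detection of linear intervention effects", with a random intercept and slope and autoregressive errors.

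The section on Web-Based Supportive Therapy says that the post-session battery is given "immediately postintervention to index immediate shifts in proximal outcomes". Table 2 schedules the PCSC and SCSC at baseline, immediately postintervention, 3 months and 9 months. Under Aim 3, Model 1 takes VR versus Web GMI as predictor and the two postintervention control scores as mediators. The decision rule there begins "If the 95% bias-corrected CI for a total indirect parameter estimate does not contain 0".

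**The concern.** The hypothesis is about a difference in change between two measurements taken within one laboratory session, before and after a programme of about 30 minutes. The declared test is about a difference in linear trend to 9 months. These are different null hypotheses, and an effect on the first need not appear in the second.

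Aim 1 justifies linearity by three assessment points. That is the CDI-2 schedule. The control scales have four points, the first two almost coincident in calendar time, so an early step fits a straight line poorly.

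Raising perceived control is the stated reason for building the VR programme. Without a declared test, the claim would rest either on a slope that measures something else or on a model path chosen after the data are seen.

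**Working it through.** **Inputs from the article.** 53 per arm and alpha .05 (Subjects, Projected Screen Failure Rate, and Power Analysis); four time points for PCSC and SCSC (Table 2); linear time, random intercept and slope, autoregressive errors (Aim 1).

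**Inputs not in the article, so assumed.** Time coding (months 0, 0, 3, 9, or wave 0, 1, 2, 3); how much of the gain remains at 3 and 9 months; variance components; SD about 1; no dropout.

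**The plan's own figure.** A noncentral F calculation for three groups, with f = d/2 = .10, .25, .40, gives N = 969, 159 and 66 (power .801, .805, .818). The stated sizes are reproduced. They concern an omnibus ANOVA and are not in question.

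**Step 1: what a linear slope does with an immediate gain d.**

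- Months: mean 3, deviations −3, −3, 0, +6, sum of squares 54. The immediate score gets the same weight as baseline. A sustained difference (0, d, d, d) has slope (−3d + 6d)/54 = d/18 per month, so a fitted 9-month change of d/2. A difference gone by 3 months (0, d, 0, 0) has slope −3d/54 = −d/18, so −d/2.
- Wave: mean 1.5, deviations −1.5, −.5, +.5, +1.5, sum of squares 5. Sustained: (−.5 + .5 + 1.5)d/5 = .3d per wave, times 3 = .9d. Gone by 3 months: −.5d/5 × 3 = −.3d.

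**Step 2: the same under the planned covariance form.** Generalised least squares was applied with four assumed sets of intercept variance, slope variance, residual variance and autocorrelation: (.6, 0, .4, 0), (.6, .1, .4, .3), (.5, .3, .4, .2) and (.3, .2, .7, .6). The table gives the fitted change over the full time range as a share of the immediate gain: least-squares value first, range over the four sets in brackets.

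| Gain left at 3 / 9 months | Months | Wave |
|---|---|---|
| 100% / 100% | +.50 (+.29 to +.50) | +.90 (+.90 to +.98) |
| 75% / 50% | .00 (−.18 to .00) | +.375 (+.375 to +.47) |
| 50% / 25% | −.25 (−.37 to −.25) | +.075 (+.075 to +.21) |
| 0% / 0% | −.50 (−.50 to −.46) | −.30 (−.30 to −.07) |

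**Step 3: chance of a significant slope contrast**, VR versus Web GMI, immediate gain d = .5, two-sided .05. Worked case (first set, months, sustained): with time scaled to 0–1 the sum of squares is 54/81 = .667; SE = √(2/53 × .4/.667) = .1505; z = .5 × .5/.1505 = 1.66; power = Φ(1.66 − 1.96) = .38.

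| Gain left at 3 / 9 months | Months: for VR | Months: against VR | Wave: for VR | Wave: against VR |
|---|---|---|---|---|
| 100% / 100% | .11–.38 | .00 | .60–.78 | .00 |
| 75% / 50% | .01–.03 | .03–.07 | .18–.22 | .00 |
| 50% / 25% | .00 | .11–.16 | .04–.07 | .01 |
| 0% / 0% | .00 | .23–.38 | .00–.02 | .03–.15 |

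**Step 4: a direct test at the immediate time point.** The SE of a baseline-adjusted comparison is SD × √(1 − r²) × √(2/53). At r = .60 and SD 1 it is .8 × .1943 = .155; z = .5/.155 = 3.22; power = .90. Over the baseline–post correlations implied by the four sets (.60 to .72), power is .90 to .96 at d = .5 and .59 to .71 at d = .34. The value .34 is the Background's growth-mindset-versus-supportive-therapy effect, so it is only a reference point for VR versus Web GMI. Without baseline adjustment, z = .5/.1943 = 2.57 and power is about .73 at d = .5.

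**The case against.** The best reply is that Aim 3 does reach the immediate effect. The condition-to-mediator path of Model 1 is the VR-versus-Web difference in immediate postintervention control. Under randomisation it estimates the hypothesised effect, with about .73 power at d = .5 even unadjusted. A reader might infer that the slope is the only analysis touching this hypothesis; the article does not support that. What remains is that the path has no decision rule of its own and no named baseline term, although the hypothesis is about increases. The rules cover specific and total indirect effects, which also depend on the control-to-depression path. A null indirect effect therefore would not show that VR failed to raise control.

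Second, time coding and persistence are unstated, and an article may leave coding to the analysis plan. A reader might infer that the slope would mostly miss a real gain, or that VR would be reported as worse. Neither holds in general. With wave coding a sustained gain is about 90% recovered. A sizeable risk of a significant result against VR needs months coding and marked fading. The Background also says that growth mindset programmes have mitigated low perceived control over time as well as in the short term, which argues against assuming full fading, though it does not concern VR versus Web GMI.

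Third, perceived control is a secondary outcome. That is correct and limits the weight of the point.

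None of this supplies the missing test. The article itself fixes the model, contrast, interaction and P<.05 reading for these scales, so the point is about what is fixed, not about detail left out.

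**Conclusion.** The point holds in this form: a stated hypothesis on immediate change has no declared test that matches it, and the one declared test of an arm difference on PCSC and SCSC targets 9-month linear change. For an immediate d = .5 that is fully sustained, the slope test finds VR superior with probability .11 to .38 (months) or .60 to .78 (wave), against .90 to .96 for a direct baseline-adjusted comparison. If the gain falls to 50% and then 25%, the slope figures are .00 and .04 to .07. The weights in months and waves are plain algebra. The probabilities rest on assumed correlations, variance components and persistence with no dropout, and should be quoted for both codings. The matter should be corrected, but it is confined to a secondary outcome and the mechanism claim: the CDI-2 is not given immediately postintervention, and neither it nor N = 159 is affected.

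**What to change.** In Aim 3, declare as the test of the first hypothesis the VR-versus-Web GMI comparison of the immediate postintervention PCSC score, and separately the SCSC score, each adjusted for its baseline score. This can be an ANCOVA, or the Model 1 condition-to-mediator path with baseline added. Apply Holm's correction over the two scales, and base any statement about a larger immediate increase in perceived control on these results. Keep the mixed model for change to 3 and 9 months, without placing the postintervention score on its linear time axis.

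The cost is a few sentences and two extra secondary tests on data already collected.
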